An adherent event is defined as taking medication within a specified time window of a dose on the previous day. For a once daily medication, an adherent event is defined as taking the medication within 24 ± 4 h of the previous day’s dose. For a twice daily medication, an adherent event is defined as taking the first medication dose within 24 ± 2 h of the previous day’s first dose and taking the second medication dose within 24 ± 2 h of the previous day’s second dose. For a three times daily medication, an adherent event is defined as taking the medication dose (first, second, or third) within 24 ± 1.3 h of the previous day’s corresponding medication dose (first, second, or third). For a four-time daily medication, an adherent event is defined as taking the medication dose (first, second, third, or fourth) within 24 ± 1 h of the previous day’s corresponding medication dose. The biological efficacy of medications dosed multiple times daily declines when not taken on time [38–40]. However, when calculating adherence for medications dosed more than once a day, we compare the current day’s doses to the previous day’s corresponding doses rather than simply the previous dose (second versus first, or third versus second) as lifestyle and sleeping patterns can result in medication times that are not equally spaced. This method of calculating adherence also allows for large shifts (time zone changes for work or vacation) or gradual changes in times when medications are taken without overly penalizing the patient, which can happen when calculating adherence relative to a median time. Additionally, this method of measuring adherence ensures that adherence credit is not given for instances where bottles are opened numerous times just prior to a clinic visit [119]. For participants on more than one medication, adherence will first be measured at the medication level and then aggregated to the person level by dividing the total number of doses of all medication(s) taken on time by the total number of doses of all medication(s) prescribed. Baseline adherence will be calculated monthly during the 3-month monitoring period. The median monthly adherence will be designated as the baseline adherence score; choosing the median will help to mitigate the effects of regression to the mean. We will exclude patients from participating in the study whose median baseline adherence score is > 80% on all of their glaucoma medications after a baseline observation period of 3 months.

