### Outcomes

#### Primary outcome

The primary outcome is change in medication adherence (continuous variable for percentage of medication doses taken on time) measured by electronic medication monitors after each intervention. We will also measure adherence by three additional techniques in order to reflect different aspects of adherence behavior [51] and compare the techniques to one another: (a) video-recorded drop instillation, (b) self-reported adherence [52–55], and (c) pharmacy refill data. To assess how well patients can properly instill their eye drops, we will video-record patients instilling their eye drops during their third and fifth study visits, before and at the end of the eyeGuide intervention, respectively. Two masked assessors will review the videos and assess each participant for the following three techniques: (1) does the participant dispense a single drop, (2) does the drop get into the eye, and (3) does the participant touch the dropper tip to the ocular adnexa or extraocular structures. Self-reported adherence will be assessed with the Morisky questionnaire [56] (eight items, Cronbach *α* = 0.83), the Adherence to Refills and Medications Scale [57] (ARMS, 12 items, *α* = 0.81), and three additional questions about adherence from the glaucoma literature [55, 51]. These adherence questionnaires will be given at the baseline, 3-, 6-, 12-, and 24-month study visits.

Pharmacy refill data will be obtained by calling each participant’s pharmacy every 3 months to identify whether each prescribed medication has been filled. The medication possession ratio (MPR) is the proportion of days during a fixed time period where the patient had an adequate supply of medication to use at the prescribed frequency. MPR will be calculated at the patient level after combining refill data from all medications during a defined time period, as follows:$$ \frac{\mathrm{MPR}=\kern0.5em \#\mathrm{days}\ \mathrm{correct}\ \mathrm{amount}\ \mathrm{of}\ \mathrm{medication}\ 1+\dots +\#\mathrm{days}\ \mathrm{correct}\ \mathrm{amount}\ \mathrm{of}\ \mathrm{medication}\ 4}{\#\mathrm{elapsed}\ \mathrm{days}\ \mathrm{medication}\ 1+\dots +\#\mathrm{elapsed}\ \mathrm{days}\ \mathrm{medication}\ 4} $$

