In this study, MPR will be calculated during fixed, quarterly time intervals of 91–92 days from enrollment, as well as cumulatively over each intervention period. The participants’ pharmacies will be called after a quarter has been completed to obtain refill information (date of fill, medication dispensed, day’s supply, number of mLs dispensed). In the event of overlapping refills, it will be assumed that medications are taken sequentially, not doubly dosed, to avoid an MPR greater than 1.

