### Statistical design

#### Data analysis

The primary outcome, adherence, captured by the electronic monitors, will be a continuous measure from 0 to 100 representing the percent of glaucoma medication doses taken on time over a specific time period. Baseline adherence for the 3-month interval before any intervention will be investigated for the Hawthorne effect. Because simply monitoring a patient can cause them to temporarily change their behavior, even in the absence of actual intervention [81], we will plot adherence over time for each patient during the first 3 months of monitoring. Previous electronic medication monitoring for glaucoma medications demonstrated that the Hawthorne effect wore off after approximately 40 days of monitoring, which is why we chose to monitor participants for 90 days [82]. We will investigate plots for patterns of better adherence during the initial weeks of monitoring and worse adherence during the later weeks of baseline monitoring. Additionally, we will compare adherence in earlier vs. later weeks using paired *t* tests. If a significant Hawthorne effect is found, we will use the third month of monitoring data as a baseline adherence score. Although using the worst month of adherence as a baseline score could expose us to regression to the mean, we would expect outliers in adherence to be random throughout the 3-month period and not necessarily bias the results in only the last month of monitoring. Adherence at baseline and after the intervention will be compared with paired *t* tests for all pair-wise comparisons. Adherence 1 year after the end of all interventions will be evaluated for stability. This will be investigated with plots, and analyzed with paired tests and linear mixed regression models (LMM).

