Secondary outcomes include comparing adherence measured by pharmacy refill data, self-report, and successful eye-drop instillation to electronic monitoring using Pearson’s correlations. Changes in glaucoma skills and energy for change will be assessed after each intervention component and at 1 and 2 years post-intervention and compared with paired *t* tests and McNemar’s tests for continuous and categorical measures. All analyses will be conducted with SAS software, version 9.4 (SAS Institute, Cary, NC, USA).

The semi-structured interviews will be recorded and transcribed verbatim. Two investigators will read the transcripts and identify major themes. The data will be interpreted qualitatively using grounded theory [86]. A code book will be generated defining codes for each theme. Two investigators will then code the transcripts. Any areas of disagreement will be discussed until consensus is reached or adjudicated by a third researcher [87]. The coded content will be tallied to weight the frequency of the themes. The transcripts will also be analyzed by participant group, those who did and those who did not improve from the intervention. Themes from these two groups will be compared in a joint display to try to identify reasons why the program was not successful among some participants to identify areas for programmatic improvement.

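### Pearson's correlation, the only method named for comparing adherence measures, cannot show whether refill adherence lies systematically above or below monitored adherence

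*Protocol article*

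**What the plan says.** Under Primary outcome, three further ways of measuring adherence are added to the electronic monitors, to capture different aspects of adherence and to "compare the techniques to one another". Under Data analysis, the comparison becomes a secondary outcome with one method for all three comparators: "Secondary outcomes include comparing adherence measured by pharmacy refill data, self-report, and successful eye-drop instillation to electronic monitoring using" Pearson's correlations. No analysis of differences in level is mentioned.

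The two measures at issue are defined as follows.

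- Monitor score: it "will be a continuous measure from 0 to 100 representing the percent of glaucoma medication doses taken on time" (Data analysis).
- MPR: it "is the proportion of days during a fixed time period where the patient had an adequate supply of medication" (Primary outcome). It is calculated in quarters of 91–92 days from enrollment and cumulatively over each intervention period. For overlapping refills, "it will be assumed that medications are taken sequentially, not doubly dosed, to avoid an MPR greater than 1".

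The entry rule is in Baseline eligibility assessment: "We will exclude patients from participating in the study whose median baseline adherence score is > 80% on all of their glaucoma medications", judged after the 3-month run-in.

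**The concern.** MPR and the monitor score are both proportions of intended use. A reader comparing them would ask two things: do they rank patients alike, and do they give the same level? Pearson's correlation addresses the first and is silent on the second.

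Level matters in this plan. The 80% mark decides eligibility, and adherence of 80% or more is the outcome of the planned repeated-measures logistic regression. As an illustration with an assumed gap, if MPR ran 25 points above the monitor, a patient monitored at 65% would be at 90% by MPR. The two measures would put that patient on opposite sides of the mark, and the correlation would not reveal it.

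A lesser matter concerns the baseline quarter. Patients with high monitored adherence have been removed from it, which narrows the range of the monitor score and tends to lower any correlation computed there. The plan does not say which period each correlation uses, so a low baseline value could be taken for a weak relation between the measures.

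**Working it through.** **The plan's own figure.** No figure is stated for the correlation analysis. The only design figure is the sample size, and it reproduces. Inputs from Sample size: difference 0.10 (0.7 to 0.8), SD 0.20, pre-post correlation 0.3, type-1 error 5% (taken as two-sided, since the side is not stated), power 80%. The SD of the paired difference is 0.20 × √(2 × (1 − 0.3)) = 0.2366. A paired t test (noncentral t) has power 0.792 at n = 45 and 0.801 at n = 46, so 46 is confirmed.

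**Step 1: what the correlation can see.** For any constant c, corr(X, Y + c) = corr(X, Y), while the mean of (Y + c − X) rises by c. A simulation with true correlations of 0.30, 0.50 and 0.70 and shifts of 0, 10, 20 and 30 points left each correlation unchanged, while the mean difference moved from 0 to 0.30. Because MPR is held at 1, a real gap would not be exactly constant across patients. That does not change the point: the coefficient contains no term for the difference in means.

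**Step 2: what the planned sample could show.** Assume SD 0.20 for both measures and a correlation between them of 0.3 to 0.5. The document gives neither the SD of MPR nor this correlation.

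- SD of the difference: 0.20 × √(2 × 0.7) = 0.237 at 0.3, and 0.20 × √(2 × 0.5) = 0.200 at 0.5.
- 95% CI half-width, t × SD/√n: 0.070 and 0.059 at n = 46; 0.063 and 0.053 at n = 57.
- Limits of agreement, mean difference ± 1.96 × SD: ±0.46 and ±0.39.

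At a correlation of 0.3 the SD is the 0.2366 of the sample-size calculation, so 46 patients have 80% power for a 10-point gap.

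**Step 3: baseline quarter only.** Assume that the monitor score among run-in patients, before the exclusion, is normal with mean μ and SD σ, is cut cleanly at 0.80, and is linearly related to the comparator with constant residual variance. With b = (0.80 − μ)/σ and λ = φ(b)/Φ(b), the SD ratio satisfies u² = 1 − bλ − λ², and the restricted correlation is r′ = r·u/√(1 − r² + r²u²).

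Example with μ = 0.70, σ = 0.20, r = 0.5: b = 0.5, λ = 0.509, u² = 0.486, u = 0.697, so r′ = 0.5 × 0.697/√(0.75 + 0.25 × 0.486) = 0.37.

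The document does not give μ or σ before exclusion, so a range is needed (true r = 0.5):

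| μ | σ = 0.15 | σ = 0.20 | σ = 0.25 |
|---|---|---|---|
| 0.50 | 0.478 | 0.453 | 0.432 |
| 0.60 | 0.442 | 0.417 | 0.400 |
| 0.70 | 0.388 | 0.373 | 0.364 |
| 0.80 | 0.329 | 0.329 | 0.329 |
| 0.85 | 0.300 | 0.307 | 0.311 |

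**Step 4: later quarters.** Selection now acts only through the plan's pre-post correlation of 0.3: u² = 1 − 0.3² × (1 − 0.486) = 0.954, u = 0.977, and r = 0.5 becomes 0.5 × 0.977/√(0.75 + 0.25 × 0.954) = 0.49. Over μ = 0.60 to 0.80 (σ = 0.20) the result is 0.489 to 0.494. Over 24 months there are eight quarters, and only the first is subject to the cut.

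**The case against.** The strongest reply is that agreement is not the stated aim. The plan wants different aspects of adherence and says only that the techniques will be compared. MPR records possession. The monitor records doses taken in a time window, such as 24 ± 4 h for a once-daily drug. A gap in level is therefore expected by definition, and limits of agreement would partly measure that. This stands as a caution on interpretation. A reader might infer that measuring refill overstatement is a declared objective that the plan fails to meet; the text does not say so. But comparing two proportions without comparing their levels leaves the comparison incomplete, and an expected gap is a reason to report its size.

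Three stronger readings are tempting and not supported.

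- **That the 80% entry rule attenuates these correlations generally.** The rule applies to the baseline score alone, and the correlations are not confined to baseline. Drop instillation is filmed only at visits 3 and 5 (months 6 and 10), outside the restricted period.
- **That 0.37 is the expected baseline value.** The 0.70 and 0.20 behind it are the plan's pre-intervention planning values, not a distribution before exclusion. A normal curve with those values would also put about 7% of patients above 100%. The rule uses a median of monthly scores and refers to all of a patient's medications, so the cut may not be clean either.
- **That Pearson's coefficient is wrong for instillation items and questionnaires.** With a yes/no item it is the point-biserial correlation, whose test is the same as a pooled t test of mean monitor score by success. Multi-item scale scores are commonly correlated this way. Neither measure shares a unit with the monitor, so a measure of association is a natural choice.

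It is also fair that a condensed article need not list every descriptive statistic, and nothing in it forbids reporting mean MPR beside mean monitored adherence. However, the article does fix the method for this comparison, and that method is blind to level.

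**Conclusion.** The point holds for MPR against the monitor score. The one method named leaves any systematic difference in level invisible, whatever its size, so the stated intention to compare the techniques is only partly met. That conclusion is algebraic and needs no distributional assumption.

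The range-restriction point is secondary and confined to the baseline quarter. A true correlation of 0.5 would appear as roughly 0.30 to 0.48 over pre-exclusion means of 0.50 to 0.85 and SDs of 0.15 to 0.25, all of them assumed. Later attenuation is negligible, given the plan's own 0.3. No fault is found with the choice of coefficient for self-report or instillation. The primary outcome, the sample size and the conclusions about the intervention do not depend on any of this.

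**What to change.** Keep the planned correlations. For MPR against monitored adherence, put both on the same scale and add, for each matched quarter, the paired mean difference with 95% confidence interval and the Bland-Altman limits of agreement. Note beside the result that MPR reflects possession and the monitor on-time dosing, so part of any gap is definitional. State which period each correlation uses, and add a note on range restriction to any correlation taken from the baseline quarter.

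No new data are needed: MPR is already calculated quarterly, and monitor adherence can be computed over any interval. The cost is a small amount of extra analysis and output.

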### Baseline eligibility assessment

Adherence will be measured electronically for 3 months prior to the first intervention to determine study eligibility and obtain a baseline, pre-intervention measure of medication adherence. The participant’s medication(s) and dosing schedule is determined by first reviewing the patient’s medical record and then confirming the medications with the patient. The study coordinator will record these data into the AdhereTech system. Participants will place their glaucoma medications inside AdhereTech electronic medication monitors that look like pill bottles. Patients will have different monitors for each of their glaucoma medications. Each time a bottle is opened, and the time and date are recorded. These records will be collected in real time and transmitted through the cellular data network so that adherence to medications can be calculated at any time interval (weekly, biweekly, monthly, etc.). The study coordinator will record each participant’s adherence data in the medical record during their study visits.

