**Fig. 3 Fig3:**
[figure not shown]
Pilot study timeline

Eligible patients will participate in five more study visits. At the third study visit, 6 months from enrollment, participants will have their first 60-min eyeGuide counseling session with the glaucoma counselor and will take a 30-min survey. Their eye drop instillation will also be video-recorded. At the fourth study visit, 8 months from enrollment, participants will have their second 30-min eyeGuide counseling session and will take a 10-min survey. At their fifth study visit, 10 months from enrollment, they will have their final 30 min eyeGuide counseling session and have their eye drop instillation technique video-recorded. The intervention will end at the sixth study visit, 12 months from enrollment, where participants will come in to take a 45-min survey and undergo a 30-min semi-structured interview to obtain qualitative feedback about the eyeGuide program. Between the in-person eyeGuide counseling sessions, the glaucoma counselor will check-in with participants by telephone to update them on their adherence and discuss any issues they are having. These check-ins will take place more frequently at the beginning of the eyeGuide intervention, at 2 week intervals, and less frequently toward the end of the eyeGuide intervention (at 1 month intervals; Fig. 3). Participants will continue using their electronic medication monitors for an additional 12 months after the intervention has ended. At the seventh and final study visit, 24 months from enrollment, participants will return their electronic medication monitors and take a 45-min survey. Participants will receive a $35 stipend for each of their seven study visits and $35 for returning their adherence monitors.

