### Personalized intervention tested in a pre-post design

#### Component 1

Participants will decide on a daily time when they would like to receive an automated reminder to take each dose of all of their glaucoma medications *if* they have not yet taken the dose. The reminder will be either an automated phone call or text message. Participants can also choose to activate an audio or visual alert [41–43]. AdhereTech will provide all of the preferred automated alerts. Participants’ adherence will be monitored throughout the 3-month period of receiving these automated reminders.

#### Component 2

After 3 months of receiving the automated reminders, participants will begin the tailored eyeGuide program. The program is tailored using computer programming so that the information each participant receives is personalized to their demographics and circumstances. The eyeGuide is tailored on the following variables: name, gender, race/ethnicity, ophthalmologist’s name, ophthalmologist’s gender, glaucoma type, past glaucoma surgeries or lasers, optic nerve photographs, visual field test results, use of the internet and/or smartphone, family support for eye drop instillation, and barriers to optimal glaucoma medication adherence.

Using the eyeGuide tablet-based tool, the glaucoma counselor will teach eye drop instillation, provide education tailored to a participant’s test results, elicit the barriers the participants face in managing their glaucoma, share tailored patient testimonials about strategies other patients used to overcome similar barriers, and brainstorm solutions together during the three in-person counseling sessions. The counselor will collaborate with participants to form an “action plan”—a short-term plan of steps to use to address identified barriers including how to integrate glaucoma medications into daily life (Fig. 2) [44–46]. The counselor will call participants once every 2 weeks between the first two eyeGuide study visits and then once monthly to provide feedback on their adherence level, check-in on their action plan, and help the participant identify new action steps. In-person counseling sessions will take place in a small Wi-Fi-enabled conference room at the Kellogg Eye Center located nearby an examination room where IOP measurement is taken.

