#### Secondary outcomes

Secondary patient outcomes include changes in clinical outcomes, changes in psychosocial mediators of adherence, and intervention impact on patient satisfaction. Our clinical outcome is IOP and IOP fluctuation [58], which will be measured during each study visit and collected from clinic visits that participants have during the study period (expect 7–9 measurements from study visits and clinic visits). IOP will be checked at each in-person study visit using Goldmann applanation tonometry. Any additional IOP measurements taken during clinic visits during participants’ time in the study will be abstracted from the electronic health record.

The two psychosocial mediators of adherence in our theoretical model (Fig. 1) include (1) change in perceived *glaucoma skills* (perceived competence [59]), glaucoma knowledge [60], glaucoma medication and eye drop instillation self-efficacy [61], goal setting [62], and propensity to ask questions of their physician [63]) and (2) change in *energy for change* (motivational state [64] and autonomy [65]) after each intervention. We will also assess the intervention’s impact on patient satisfaction (satisfaction with information about glaucoma [66] and client satisfaction [67, 68]).

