Validated measures will be used to assess these proposed mediators of adherence. Skills will be measured with five constructs: perceived competence, glaucoma knowledge, self-efficacy, goal setting, and confidence asking the physician questions. Perceived competence [59] (four items, Cronbach *α* = 0.80) assesses participants’ perceptions of how able they are to manage their glaucoma on a seven-point Likert scale. Perceived competence will be measured at the baseline, 6-, 12-, and 24-month study visits. Glaucoma Knowledge will be assessed with a 10-item true/false test generated by the National Eye Institute (NEI) [60]. Glaucoma knowledge will be measured at the 3- and 8-month study visits, before and after the eyeGuide intervention, respectively, and at the 24-month study visit. Glaucoma medication and eye drop instillation self-efficacy [61] (medication self-efficacy, 10 items, eye drop instillation self-efficacy, 6 items, *α* = 0.91 for all 16 items) assess participants’ self-confidence in using their eye drop medications as prescribed and instilling them into their eyes correctly using a three-point Likert scale. Glaucoma medication and eye drop instillation self-efficacy will be measured at the baseline, 6-, 12-, and 24-month study visits. Goal setting (three items, *α* = 0.80) measures whether or not health care providers asked participants to set goals to improve how they take care of their chronic disease on a five-point Likert scale. The Goal Setting Scale is a sub-scale of the Patient Assessment of Chronic Illness [62] measure. We could not use the full sub-scale as the final two questions ask if the person has been asked to attend a class to help cope with their chronic condition or asked to fill out a survey about their chronic condition, neither of which are standard aspects of current glaucoma care. Goal setting will be measured at the baseline study visit, and the 12- and 24-month study visits. Confidence asking the physician questions will be measured with three items from the adapted Perceived Efficacy in Patient-Physician Interactions Scale [63] (PEPPI, five items, α = 0.83) using a five-point Likert scale. Confidence asking the physician questions will be assessed at the baseline visit and the 12-month study visit.

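### Change in skills is promised after each intervention component, but goal setting and confidence asking questions have no measurement between month 0 and month 12, so neither component has its own contrast

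*Protocol article*

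**What the plan says.** The analysis commitment is in the Data analysis section: "Changes in glaucoma skills and energy for change will be assessed after each intervention component". The same sentence adds later post-intervention assessments and names paired t tests and McNemar's tests. The Secondary outcomes section uses similar language, ending its list of mediators with "motivational state [64] and autonomy [65]) after each intervention".

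The Secondary outcomes section then defines the term: "Skills will be measured with five constructs: perceived competence, glaucoma knowledge, self-efficacy, goal setting, and confidence asking the physician questions". It fixes the visits for each construct. For the two at issue: "Goal setting will be measured at the baseline study visit, and the 12- and 24-month study visits", and "Confidence asking the physician questions will be assessed at the baseline visit and the 12-month study visit".

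The component boundaries come from three places:
- Baseline eligibility assessment: "Adherence will be measured electronically for 3 months prior to the first intervention".
- Component 2 description: "After 3 months of receiving the automated reminders, participants will begin the tailored eyeGuide program".
- Timeline: "At the third study visit, 6 months from enrollment, participants will have their first 60-min eyeGuide counseling session". The same section gives a 30-minute survey at that visit and ends the intervention at the month-12 visit.

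**The concern.** A paired test of change after a component needs a value before that component and a value at its end. With two components given one after the other, the value at the changeover (month 6) serves both: it closes the reminder period and opens the eyeGuide period. If it is missing, the planned tests for that construct have no data, and no analysis of the collected values can supply them.

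At stake is what the pilot can say about these two proposed mediators. The components are deliberately ordered by how much resource they need, so a natural question before a randomized trial is whether counseling moves skills beyond what reminders do. For goal setting and confidence, the schedule cannot inform that question.

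**Working it through.** The plan states no figure on this point that could be reproduced; the check compares the promised contrasts with the measurement schedule.

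**Step 1: component periods.** Run-in is months 0 to 3, reminders months 3 to 6, and eyeGuide months 6 to 12. The lengths add up to the month-12 visit: 3 + 3 + 6 = 12.

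**Step 2: schedule by construct** (Secondary outcomes section).

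| Construct | Months measured | Strictly between 0 and 12 | Month 6 value |
|---|---|---|---|
| Perceived competence | 0, 6, 12, 24 | 6 | yes |
| Medication and instillation self-efficacy | 0, 6, 12, 24 | 6 | yes |
| Glaucoma knowledge | 3, 8, 24 | 3, 8 | no |
| Goal setting | 0, 12, 24 | none | no |
| Confidence asking the physician | 0, 12 | none | no |
| HCCQ (energy for change) | 0, 6, 12, 24 | 6 | yes |
| TSRQ (energy for change) | 0, 6, 12, 24 | 6 | yes |

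Goal setting and confidence are the only two with nothing between month 0 and month 12. Glaucoma knowledge also lacks month 6, but its timing problem is of a different kind and is not counted here. Table 2 of the article does not list goal setting or confidence, so it adds no further time points.

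**Step 3: what can be estimated.** Write Y(m) for the score at month m. Then

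Y(12) − Y(0) = [Y(3) − Y(0)] + [Y(6) − Y(3)] + [Y(12) − Y(6)]

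= run-in change + reminder-period change + eyeGuide-period change.

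Only the left-hand side is observed for these two constructs; none of the three terms on the right is.

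| Contrast | Goal setting | Confidence |
|---|---|---|
| After reminders (needs month 6) | cannot be computed | cannot be computed |
| eyeGuide, month 12 minus month 6 | cannot be isolated | cannot be isolated |
| Follow-up, month 24 minus month 12 | available | cannot be computed |

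So two of three contrasts fail for goal setting, and all three fail for confidence.

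**Step 4: the follow-up wording.** The Data analysis sentence places the later assessments at one and two years post-intervention. Counted from the end of the intervention, these are months 12 + 12 = 24 and 12 + 24 = 36, and month 36 lies beyond the final visit at month 24. Counted from enrollment, they are months 12 and 24. Under either reading, confidence has no value after month 12.

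**Step 5: what a month-6 value would give.** With Y(6) added, Y(12) − Y(6) is observed, and so is Y(6) − Y(0) = [Y(3) − Y(0)] + [Y(6) − Y(3)]. The first is the change over the eyeGuide period alone. The second still combines run-in with reminders. The four scales already measured at months 0, 6, 12 and 24 have this same limit.

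**The case against.** The strongest reply is that this is a small inconsistency in an uncontrolled pilot. The component-wise aim is chiefly about medication adherence, which the electronic monitors record continuously and which this gap does not touch. Effects on the psychosocial mediators are described as exploratory. Four other scales have a month-6 value, and goal setting keeps its month-24 follow-up. All of this stands and limits the importance of the point; a reader who concludes that the comparison of the two components as a whole is undermined goes further than the document allows.

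A second reply is grammatical. In the Secondary outcomes section, the phrase about each intervention could attach to energy for change alone, whose two scales do have the right schedule. That is a fair reading there. The Data analysis sentence, however, names glaucoma skills explicitly and exempts no construct.

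A third reply is that reminders may not be expected to change goal setting or confidence. The document does not say so; if that was the intent, the analysis sentence should be narrower.

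A reader might also infer that the plan would credit the whole month 0-to-12 change to one component. Nothing in the text does that: it specifies paired tests, and its mediator models regress the mediator on time for the intervention as a whole. What follows is a planned contrast without data, not a stated misattribution.

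Finally, a month-6 value does not separate everything, as step 5 of the working shows. And because registration was retrospective, some participants may already be past month 6. Both points are right, and the fix allows for them.

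**Conclusion.** The point holds as a contradiction between the analysis sentence and the measurement schedule. For two of the five skills constructs, goal setting and confidence asking the physician questions, no component-specific change can be estimated; only a 12-month change pooling run-in, reminders and eyeGuide is available. For confidence, no comparison after the end of the intervention is possible either.

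This should be corrected, but it is not critical: it concerns two three-item scales among the secondary outcomes and leaves the primary outcome intact. The conclusion assumes that the visits stated in the Secondary outcomes section are complete for these two scales. The timeline figure was not available for checking, but the text states the visits outright. No assumption about effect size, variance or dropout is needed.

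**What to change.** Add the three goal-setting items and the three confidence items to the existing month-6 survey, completed before the first eyeGuide session. The month 6-to-12 change then covers the eyeGuide period alone. Label the month 0-to-6 change as run-in plus reminders, not as a reminder effect. Add the three confidence items to the month-24 survey.

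Where participants are already past month 6 or the items cannot be added, limit the per-component statement in the Data analysis section to constructs measured at month 6. Report goal setting and confidence as whole-programme change from month 0 to 12, with no component-specific claim. In the same sentence, restate the follow-up times so that they fit a study ending at month 24.

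The cost is six items in a 30-minute survey and three in a 45-minute survey, or otherwise one revised sentence and a narrower secondary claim.
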